### Mindfulness-based cognitive therapy (MBCT)

We will utilise the standard MBCT treatment protocol [21]. Each session combines key elements of cognitive therapy with training in mindfulness meditation. Participants are taught skills designed to foster present moment awareness which include practising mindfulness meditation, body scan, mindful walking and stretching. Cognitive therapy techniques include education about the role of negative thoughts and how rumination, avoidance, suppression, and struggling with unhelpful cognitions and emotions can perpetuate distress rather than resolve it. Participants learn to identify patterns of emotional response and negative thinking that act as warning signals for NSSI and help one another to develop crisis plans and actions to take in the event of future NSSI urges.

### Supportive therapy (ST)

Supportive therapy is a widely used active control condition in psychotherapy outcome studies, as it controls for both the non-specific effects of any psychological intervention (i.e. therapeutic relationship) and the unique aspects of group therapy (i.e. social support). Additionally, from an ethical perspective, the group support condition ensures that no participants are left without an intervention. We will use Borkovec and Costello’s [33] manualised protocol. In ST, the therapist provides empathy, fosters a supportive environment, and facilitates discussions among group members around NSSI and other life issues. No MBCT techniques are taught by the therapist.

### Ethical issues

After initial telephone screening to assess eligibility, during which participants are verbally informed of the study requirements, all participants will be provided with a detailed information sheet which outlines the aims and participation requirements of the study, informs participants of the confidential and voluntary nature of participation, and outlines how data are to be collected, used and stored in accordance with relevant Privacy Legislation. All participants will be afforded the opportunity to ask questions about the study and will provide signed consent to participate in the research project. Participants are free to withdraw from the research project at any time.

There is some concern regarding the potential for social contagion when discussing NSSI in a group setting. Our experience and a growing evidence base, suggests that when appropriately addressed, iatrogenic effects are rarely observed [34]. Conversely, research indicates that participants benefit from being asked about their NSSI [35, 36]. We will minimise risk of iatrogenic effects by following established guidelines to reduce social contagion [37], including discouraging sharing of explicit details, NSSI images or scars in the group setting. This conduct of this trial has been approved by the Curtin University Human Research Ethics Committee (Ref number: 4884).

#### Clinical outcome measures

##### Self-injury monitoring diary:

Participants will complete the Self-Injury Monitoring Diary, developed for this study, across the course of the trial, to assess ongoing frequency and medical severity of NSSI. Each day participants will indicate whether they had an urge to self-injure, the strength of this urge, whether they did self-injure, and the severity of the injury.

##### Clinician-rated severity of Non-suicidal self-injury

[27]: This single item scale assesses the severity of NSSI on a scale of 0 = None; 1 = Sub-threshold; 2 = Mild; 3 = Moderate; and 4 = Severe. The measure was designed to capture clinically meaningful changes in NSSI severity, based on the proposed DSM-5 criteria [8]. Therapists will rate each participant at the end of each therapeutic session.

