## Methods/Design

### Study design

We will conduct a parallel group randomised controlled design in which half our participants receive Group Mindfulness Based Cognitive Therapy and half receive Group Supportive Therapy. We will implement a computerised block randomisation procedure to ensure equal distribution of participants across conditions (Fig. 2). As far as practically possible participants will be blind to group allocation. Self-report, behavioural and physiological measures will be administered at pre-treatment, mid-treatment, post-treatment, and 3 and 6-month follow-up. To maximise external validity, a minimum follow-up period of 6 months is recommended and will be adopted in the present study [26]. Baseline assessments and follow up assessments will be conducted by a researcher blind to group allocation.

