### Intervention

A trained psychologist will conduct telephone interviews to assess eligibility with the single-item Clinician-Rated Severity of Non-Suicidal Self-Injury [27] and 6-item Mini International Psychiatric Interview [28]. Both treatment conditions will comprise 8 weekly group sessions of 2 h duration with up to 12 participants in each group. All group sessions and assessments will occur at the Curtin University Psychology Clinic. As per standard practice, two trained therapists, blind to the results of baseline and follow-up assessments, will facilitate each group. Suicidality will be monitored weekly throughout treatment (both conditions) using the 3-item Self-Monitoring Suicide Ideation Scale [29].

To ensure treatment fidelity, each therapist will receive training and weekly supervision. All treatment groups will be audiotaped with 10 % checked to ensure adherence to manualised treatment protocols, using the Mindfulness Based Cognitive Therapy Adherence Scale for MBCT group [30]. At the first treatment session all participants will complete the 6-item Credibility/Expectancy Questionnaire [31] to assess treatment face validity. We will assess treatment acceptability using Dear et al’s [32] 4-item acceptability rating scale. Upon completion of treatment, participants will also provide open comments about acceptability, and specify intended NSSI prevention strategies.

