## Discussion

Although delineated from suicidal behaviour by definition, people who repeatedly self-injure carry a fourfold risk of suicidal thoughts and behaviours within the following year [7], and are 42 times more likely to attempt suicide [2]. Of note, NSSI increases risk of suicidal behaviour over and above risk conferred by comorbid psychopathology, adverse life events and psychosocial risk factors [7, 62]. To reduce the physical, psychological, social and economic burden of self-injury, effective interventions are urgently needed [63]. MBCT is a transdiagnostic intervention that has established evidence in the treatment of many clinical conditions. Importantly, MBCT was designed specifically to focus on the very mechanisms thought to maintain self-injury (i.e. rumination, focus on negative thoughts, poor emotion regulation). MBCT thus offers untapped potential for reducing the frequency and medical severity of self-injury.

This trial offers significant advantages over previous efforts to determine effective treatments for NSSI. First, the components of MBCT directly align with cognitive and emotional factors related to NSSI, thus offering the best chance of targeting the key mechanisms maintaining the behaviour. Second, we will collect both self-report and clinician ratings of NSSI severity through the course of the project. These will be supplemented with behavioural measures of attentional bias and analysis of cortisol as a physiological measure of stress. These objective measures significantly strengthen the scientific rigour of the findings. Third, the active comparison condition allows additional control over the influence of group processes, therefore allowing a direct test of the specific intervention mechanism of MBCT.

While the proposed sample size is small, the repeated measures design ensures our study is sufficiently powered to identify medium effects on our primary outcome variable, and provide preliminary assessment of the mechanisms of change. Restricting our sample to 18–25 years necessarily will limit generalisation of the findings to other age groups, however given this is the age at which NSSI is most common [2] it seems the appropriate age range to first test the efficacy of MBCT in reducing this behaviour.

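### The clinician-rated NSSI severity item is scored by therapists who know the arm, with no rating specified at 3 or 6 months, although a blinded assessor is already in place

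*Protocol article*

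**What the plan says.** Under the clinical outcome measures, the protocol article describes a single-item clinician-rated severity scale for NSSI, scored from 0 (none) to 4 (severe). It names the rater and the timing: "Therapists will rate each participant at the end of each therapeutic session". The Intervention section sets the length of treatment: "Both treatment conditions will comprise 8 weekly group sessions of 2 h duration". It describes the therapists' blinding as "two trained therapists, blind to the results of baseline and follow-up assessments, will facilitate each group". That covers assessment results, not allocation. The Supportive therapy section says of that arm: "No MBCT techniques are taught by the therapist".

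The Study design section provides an independent assessor: "Baseline assessments and follow up assessments will be conducted by a researcher blind to group allocation". Its schedule reads: "Self-report, behavioural and physiological measures will be administered at pre-treatment, mid-treatment, post-treatment, and 3 and 6-month follow-up". Clinician ratings are not in that list.

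The same item has one other stated use, at screening: "A trained psychologist will conduct telephone interviews to assess eligibility with the single-item Clinician-Rated Severity of Non-Suicidal Self-Injury".

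The Discussion counts among the trial's advantages that "we will collect both self-report and clinician ratings of NSSI severity through the course of the project".

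**The concern.** A 0-to-4 global judgement leaves room for expectation. When the person who delivers the therapy makes it, knowledge of the arm coincides completely with the arm itself. A difference in rating habit between MBCT and supportive-therapy therapists then cannot be told apart from a treatment effect, and no analysis can separate the two afterwards.

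The timing adds a second problem. Ratings attached to sessions end when the sessions end. The first hypothesis expects the NSSI reduction to last to 3 and 6 months, and the statistical section plans to classify clinically significant NSSI change at post-treatment and follow-up. As described, the only clinician-rated NSSI measure contributes nothing at the two later visits.

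**Working it through.** **Who rates, and what they know.** The therapists rate. They are blind to assessment results only. The two arms follow different manuals with different session content, so anyone leading a group knows which treatment it is. The article does not say this outright; it follows from the therapist's task.

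**When ratings occur.** There are 8 weekly sessions with a rating at the end of each, so at most 8 therapist ratings per participant, all within the treatment period. No session is described at 3 or 6 months, so the stated schedule covers 0 of the 2 later visits. The list of measures for the scheduled assessments names self-report, behavioural and physiological measures, so it does not fill the gap. The Discussion's claim of clinician ratings through the project has no stated source once treatment ends.

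**What else measures NSSI.** The self-injury monitoring diary is completed daily by participants across the trial, and its stated purpose is to assess frequency and medical severity. The primary outcome in the Abstract is described in the same terms. The clinician item is described as a severity scale built on the proposed DSM-5 criteria, without the word medical. The article does not say which instrument defines severity for the primary analysis.

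**The sample-size figure used below.** The article states 40 per group for a medium effect, power 0.80 and α 0.05. A repeated-measures between-group F test reproduces it, with these assumptions that are not in the article: f = 0.25 for medium, correlation ρ = 0.5 between time points, and m = 4 or 5 time points.
- Noncentrality λ = N·f²·m / (1 + (m − 1)ρ), with 1 and N − 2 degrees of freedom.
- m = 5, N = 80: λ = 80 × 0.0625 × 5 / 3 = 8.33, power 0.814; the smallest N is 78 (39 per group).
- m = 4, N = 80: λ = 80 × 0.0625 × 4 / 2.5 = 8.0, power 0.798; the smallest N is 82 (41 per group).

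The figure serves here only as the n for an illustration. Nothing in this point requires it to change.

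**Illustration of a rating shift.** Suppose there is no true effect, and therapists in one arm rate b points lower on average than those in the other. Assume SD = 1 on the 0-to-4 scale, so points and SD units coincide. Take n = 40 per arm and one two-sided 5% normal comparison.
- Noncentrality δ = b·√(n/2) = b·√20 = 4.472·b.
- P(significant) = P(Z > 1.96 − δ) + P(Z < −1.96 − δ).

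| b (SD) | δ | P(significant) |
|---|---|---|
| 0.1 | 0.45 | 0.07 |
| 0.25 | 1.12 | 0.20 |
| 0.3 | 1.34 | 0.27 |
| 0.5 | 2.24 | 0.61 |

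Both the SD and b are assumed; the article gives neither. The table shows how sensitive the comparison would be to a given shift, not how large the shift will be. It models a single comparison, whereas the article plans a mixed model for repeated measures. Averaging repeated ratings reduces random error but leaves a systematic shift in place, so the mixed model does not remove the problem.

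**The case against.** The strongest reply is that this is a supplementary measure. The diary is described in the same terms as the primary outcome and runs across the trial, so medical severity, and its maintenance at 3 and 6 months, has a stated data source without therapist ratings. That stands, and it limits the point to the clinician-rated item. A reader might infer that detection bias falls on the severity half of the primary outcome, or that the first hypothesis cannot be tested at follow-up. The article supports neither: it does not make this item the primary severity measure, and it does not tie that hypothesis to it.

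A reader might also infer that therapist rating contradicts the blinding statement. It does not. That statement covers baseline and follow-up assessments, and end-of-session ratings are neither. This is a weak design choice, not a contradiction.

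A third tempting inference is that the move from screening psychologist to therapist distorts change from baseline. The screening rating is stated for eligibility, and nothing makes it the analysis baseline. The change of rater also occurs in both arms, so by itself it does not bias the comparison.

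It is also fair to say that the article does not exclude clinician ratings by others at follow-up, and that a condensed article may leave such detail to a fuller document. But it does state who rates this item and when, and the Discussion's claim goes further than that schedule. The passages need to be reconciled whichever was intended.

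**Conclusion.** The concern holds for the clinician-rated NSSI severity item. It is a listed clinical outcome, its raters know the arm, and its stated schedule reaches neither the 3- nor the 6-month visit. A between-arm difference on it would be open to detection bias and, as written, could not show maintenance.

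The reach is limited: the diary supplies frequency and medical severity across the trial, and an effect on the whole primary outcome is not shown. The size of the bias cannot be derived from the article. The 20% and 61% figures hold only under SD 1 and assumed shifts of 0.25 and 0.5 points.

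The conclusion rests on one inference, that therapists know which treatment they deliver, and on reading the stated schedule as complete. This is an inexpensive improvement, best made before ratings begin because unblinded ratings cannot be repaired afterwards.

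**What to change.** - Have the allocation-blind researcher, trained on the item, rate it at baseline, post-treatment, 3 months and 6 months. Add mid-treatment if that visit is also blinded. The blinding statement names only baseline and follow-up, so confirm that it covers post-treatment.
- Use only these ratings in between-arm efficacy analyses of the item.
- Keep the therapists' session ratings for process monitoring and say that they are not efficacy data.
- Reconcile the Study design schedule, the description of the item and the Discussion's statement about clinician ratings, so that all three give the same raters and time points.

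The cost is one extra item at assessments already planned, plus brief rater training. The screening interview uses a trained psychologist for this item, so the researcher's suitability to rate it should be checked. The trial gives up the weekly therapist series as efficacy data. The sample size does not change.

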##### Beck depression inventory

- 2^nd^ Edition [38] (BDI-II): The BDI-II is a 21-item measures of depressive symptoms, each rated on a four-point scale. Both a continuous measure indicating severity of symptoms, and clinically meaningful cut-off scores can be obtained. The BDI-II is the gold-standard questionnaire assessment of depression and demonstrates acceptability as a screening tool in both healthy and clinical populations [39, 40].

##### Beck anxiety inventory

[41] (BAI): The BAI is a 21-item assessment of anxiety symptoms experienced in the last week, with each symptom rated on a four-point scale. Both cognitive and somatic symptoms are assessed. As the gold standard questionnaire assessment of anxiety, the BAI demonstrates excellent psychometric properties [41].

#### Mechanism of change measures

##### Cognitive and affective mindfulness scale - revised

[42] (CAMS-R): The CAMS-R is a brief (12 item) self-report measure designed to assess the capacity an individual has to be mindful. The measure demonstrates internal consistence and convergent validity with similar measures when administered to university students [42].

##### Ruminative thought style questionnaire

[43] (RTSQ): The RTSQ is a 20-item measure describing positive, negative and neutral facets of global rumination (e.g., “I can’t stop thinking about some things” or “I have never been able to distract myself from unwanted thoughts”). Respondents rate each statement on a 7-point Likert scale (1 = *not at all descriptive of me*, 7 = *describes me very well*). The RTSQ has demonstrated good convergent validity with the Response Style Questionnaire, the Global Rumination Scale and the Beck Depression Inventory, adequate test-retest reliability and high internal consistency [43].

##### Difficulty in emotion regulation scale

[44] (DERS): The DERS uses 36 items to tap into 5 aspects of emotion regulation: non-acceptance of emotional response, difficulty in goal directed behaviour, impulse control, emotional awareness, lack of emotion regulation strategies and emotional clarity. Participants respond to each item on a 5-point scale. The measure demonstrates acceptable reliability in university students as well as content and convergent validity [44].

##### Distress tolerance scale

[45]: This 14 item self-report measure assesses an individual’s ability to withstand feeling distressed. The scale assesses an individual’s ability to tolerate emotions, their appraisal of emotional situations, how absorbed they are by negative emotion and emotion regulation using 5-point Likert scales.

##### Perceived stress scale

[46]: The Perceived Stress Scale is a 10-item assessment designed to provide a global assessment of perceived stress. Items assess how unpredictable, controllable and overloaded individuals find their lives, without reference to specific events. The scale evidences discriminant validity with depression, and internal consistency [46].

##### Cortisol measurement:

Both cortisol awaking response (CAR) and daily slope (DS) will be assessed to obtain total daily cortisol output. Cortisol is a biomarker of stress and anxiety [47], and varies in response to stress among people who self-injure [48, 49]. Following best practice [50] we will collect saliva on two consecutive days at each data collection point. On each of these days, participants will collect saliva upon waking, 30 and 45 min after waking (CAR) and again at 4, 9, and 13 h after waking (DS). To increase adherence to the protocol participants who comply with at least 80 % of saliva collection will receive a $50 iTunes voucher. Participants will use Sarstedt Cortisol Salivettes® to collect saliva, which provides an easy and hygienic collection method, further encouraging compliance. Saliva is obtained by chewing on a synthetic swab which is then placed in the container for safe transportation to the laboratory for analysis. Importantly, the Salivettes® are designed to allow reliable analysis from small saliva volumes and low cortisol levels. Following collection, we will recover the saliva from the Salivettes®, centrifuge and store in aliquots at −80 °C until analysis using an enzyme-linked immunosorbent assay (ELISA). Participants will record waking time and all sampling times, and bring their clearly labelled samples to the subsequent assessment session in the clinic.

##### Attentional bias

The differential allocation of attention to emotional stimuli can be assessed in simple reaction time tasks that are presented using a computer. One of these tasks is the so called ‘dot probe’, which assesses the effect of emotional cues on the detection or identification of a probe stimulus [51]. In this task, two pictures or two words that differ in emotional valence (cues; pleasant and neutral or unpleasant and neutral) are presented simultaneously for a short period of time in different locations on a computer screen, left and right half or upper and lower half. After 500 ms, a probe stimulus is presented in the location that was previously occupied by one of the cues. The probe used in our task are two dots either arranged horizontally ‘**..**’ or vertically ‘**:**’. The participant’s task is to indicate the arrangement of the dots by pressing one of two buttons. Participants will be faster to respond to the probe if their focus of attention is at the location at which the probe is presented. If participants are faster to respond to probes that replace unpleasant cues, we conclude that attention is biased towards the unpleasant stimuli indicating preferential processing. If participants are faster to respond to probes that replace neutral cues, we conclude that attention is biased away from unpleasant stimuli indicating avoidance. Pleasant stimuli are included to assess whether the differential allocation of attention is driven by cue valence (differs for pleasant and unpleasant cues relative to neutral cues) or emotional arousal (is similar for pleasant and unpleasant cues relative to neutral cues).

Cues will be pictures (neutral, pleasant, unpleasant, NSSI related) drawn from the standardised International Affective Picture System [52] and normed words (neutral, pleasant, unpleasant, NSSI related) [53]. Cue location will be counterbalanced (e.g. pleasant cues will appear equally often in each possible location) as will be relation of probe to cue (i.e., the probe will follow an emotional cue equally often than a neutral cue - so cues are not predictive of probe position). This results in 24 different stimulus configurations (trials) for a fully counterbalanced design (3 × 2 × 2 × 2; cue valence [pleasant, unpleasant, NSSI related] x cue location [top vs. bottom/left vs right] x probe location [emotional, neutral] x stimulus material [words, pictures]). These 24 stimulus configurations will be repeated 10 times in a random order yielding a total of 240 trials. Including practise trials, this procedure will take approximately 10 min.

